#### Delivery

The implant is delivered on a custom catheter fabricated from materials with a long history of biocompatibility (medical grade PEBAX and high density polyethylene tubing and PTFE-coated stainless steel wire). The sterile catheter is approximately 3 meters long to facilitate delivery of the implant through the mouth into the jejunum. The catheter is designed to be sufficiently flexible to track through the intestine without kinking. Implantation and removal of the EndoBarrier device requires fluoroscopic x-ray guidance to determine the position of the device. Videos and photos of

|                                                                                   |                                                                                                  |                                           |                                                             |                                                  |
|-----------------------------------------------------------------------------------|--------------------------------------------------------------------------------------------------|-------------------------------------------|-------------------------------------------------------------|--------------------------------------------------|
| [figure not shown] | Title:
EndoBarrier TM
Gastrointestinal Liner
Diabetes Trial | Protocol No:
Version 5.0 | Sponsor:
Imperial College
London | Date:
5th March 2018 |
|-----------------------------------------------------------------------------------|--------------------------------------------------------------------------------------------------|-------------------------------------------|-------------------------------------------------------------|--------------------------------------------------|

the fluoroscopy images are recorded to help the investigators make treatment decisions and may be passed on to the study sponsor. The images will not contain any patient identifiable data but will be labelled with initials and study participation number only. Mean fluoroscopic x-ray time for insertion is 7 minutes (range 1-20 minutes). The constraint (maximum effective dose) for the whole procedure (implant and explant) is 9 mSv which is equivalent to 3.3 years natural background radiation in the UK (2.7mSv/year background) and results in a cancer risk of 1 in 2200 for a healthy 40 year old (5% per Sv risk factor).

## Removal

The EndoBarrier Gastrointestinal Liner will be removed at study visit 11 with a custom grasper that passes through the working channel of a standard gastroscope. The gastroscope which is fitted with a foreign body retrieval hood is used to locate the implant. The grasper is passed through the working channel of the gastroscope and used to grab the polypropylene tether located on the proximal portion of the anchor. The proximal end of the anchor is collapsed by pulling on the tether and the anchor is then pulled into the foreign body hood. Once the collapsed anchor is in the hood, the implant is removed by withdrawing the gastroscope through subject's mouth.

During explant of the EndoBarrier device eight gastric and small bowel biopsies will be taken using a standard biopsy forceps after the device has been removed. Four biopsies will be used for histology - placed in a specimen pot containing formalin and sent to St Mary's pathology lab for analysis. Four biopsies will be used for RNA extraction to perform genome-wide expression analysis – stored in Allprotect Tissue Reagent for future analysis.

All subjects will be seeing a gastroenterologist or equivalent supervised healthcare specialist at study visit 2, 6, 7, 9, 11, 12 and 15 (visit 13 on request) to discuss their well-being and any questions regarding their EndoBarrier implant.

## Diabetic Medications Titration Schema

Patients in the EndoBarrier treatment arm will also be seen by the diabetologist/endocrinologist for diabetes review at visits (2, 6, 7, 9, 11, 12, 13 and 15).

**Titration for Sulfonylureas:** Subjects must have their dose of sulfonylureas reduced by 50% at the time of implant to avoid potential hypoglycaemic episodes. If a hypoglycaemic episode is experienced their sulfonylureas must be reduced by 50% again or discontinued if the subject is on the lowest dose.

**Titration for Metformin:** Dosages of metformin will remain unchanged throughout the trial unless the sulfonylureas have already been discontinued and a subject's fasting blood glucose is documented under 5.6 mmol/L on 3 consecutive days. If the fasting blood glucose is under 5.6 mmol/L, metformin can be discontinued. If the fasting glucose is below 3.5 mmol/L then metformin should be discontinued. See section 5.1 regarding blood glucose measurements.

If hypoglycaemic episodes are experienced, it is at the Investigator's discretion to modify or discontinue metformin.

|                                                                                   |                                                                                                  |                                           |                                                             |                                                  |
|-----------------------------------------------------------------------------------|--------------------------------------------------------------------------------------------------|-------------------------------------------|-------------------------------------------------------------|--------------------------------------------------|
| [figure not shown] | Title:
EndoBarrier TM
Gastrointestinal Liner
Diabetes Trial | Protocol No:
Version 5.0 | Sponsor:
Imperial College
London | Date:
5th March 2018 |
|-----------------------------------------------------------------------------------|--------------------------------------------------------------------------------------------------|-------------------------------------------|-------------------------------------------------------------|--------------------------------------------------|

Rescue Therapy: The decision whether a subject has inadequate glycaemic control during the course of the study, sulfonylurea will be increased or insulin will be started should be made at the Investigator's discretion. This will be performed by giving a glucose meter to patients. These subjects are to receive appropriate intervention at the Investigator's discretion. After removal, subjects are to continue their diabetic medication regimen. It is recommended that subjects have their dose of sulfonylureas increased or re-introduced if previously withdrawn during the course of the study if HbA1c > 7.0%. It is also recommended if, on three successive self-tests, fasting blood sugar is > 8 mmol/l and/or post prandial glucose is > 12 mmol/l. If titrating medications back to study baseline levels is deemed to be ineffective, subsequent interventions are at the Investigator's discretion. Any changes in medication will be discussed with the Imperial College Diabetologist coordinator.

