## 5 VISIT PROCEDURES, MEASUREMENTS AND ASSESSMENTS

### 5.1 Recruitment and Screening

*Participants will be identified from a number of areas which include:*

- **Registers of patients with diabetes who have consented to be contacted about future research including DARE (Diabetes Alliance for Research in England REC 2002/7/118)**

The team responsible for a register will search the system to identify suitable participants and send out an invitation letter and participant information sheet. Interested patients will be asked to contact the research team directly to find out more about the study. No patient details will be passed on to the study team.

- **Hospital or GP patient databases/notes review (Research Site or Participant Identification Centre)**

This activity will be completed by the routine care team. The medical records may be reviewed by members of the routine care team to pre-screen whether the patient may potentially be eligible for the study before the patient is approached about the study by a member of the routine care team (hospital or GP).

|                                                                                   |                                                                                                  |                                           |                                                             |                                                  |
|-----------------------------------------------------------------------------------|--------------------------------------------------------------------------------------------------|-------------------------------------------|-------------------------------------------------------------|--------------------------------------------------|
| [figure not shown] | Title:
EndoBarrier TM
Gastrointestinal Liner
Diabetes Trial | Protocol No:
Version 5.0 | Sponsor:
Imperial College
London | Date:
5th March 2018 |
|-----------------------------------------------------------------------------------|--------------------------------------------------------------------------------------------------|-------------------------------------------|-------------------------------------------------------------|--------------------------------------------------|

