## 5.5 Description of procedures and measurements

### 5.5.1 Diabetologist/Endocrinologist Diabetes Review

The standard medical therapy arm will be carried out in accordance with the guidelines of the American Diabetes Association (see figure 2 for summary algorithm). These guidelines have been chosen as they are applicable to an International audience and thus would adhere to the current best worldwide practice that would still be likely to be relevant when the results are published following study completion.

Diabetes reviews appointments with a Diabetologist/Endocrinologist will be performed with the control arm patients at visits 2, 4, 6, 7, 9, 11, 12, 13 and 15. Diabetes reviews appointments with a Diabetologist/Endocrinologist will be performed with the EndoBarrier arm patients at visits 2, 6, 7, 9, 11, 12, 13 and 15. Blood glucose concentrations obtained as part of study-scheduled routine blood tests will be used alongside self-measurements and self-reporting of blood glucose concentrations by patients or their GP's to adjust medication regimens. Home blood glucose meter readings will be indicated, as in routine clinical practice, when patients are clinically suspected or at risk of hypoglycaemic episodes (e.g. when commenced on sulphonylurea) or when glucose readings are required for further titration of therapy.

A summary of general recommendations for anti-hyperglycaemic therapy in type 2 diabetes patients have been outlined below (Figure 2) according to the American Diabetes Association (ADA) and the European Association for the Study of Diabetes (EASD).

All female patients will also be asked to report the last date of their menstrual period, the length of their cycle and the length of their menstruation (bleeding) at screening visit, visit 2, 4, 6, 7, 9, 11, 12, 13 and 15. This information will be used to ensure they are not pregnant and it will also help to monitor any changes in their menstrual cycle during the course of the study.

|                                                                                   |                                                                             |                                    |                                               |                                            |

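### The metformin titration rule for the device arm gives opposite instructions for a fasting glucose below 3.5 mmol/L, and its pointer to the glucose-measurement text is wrong

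*Protocol*

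**What the plan says.** The rule is in protocol section 5.5.2, Diabetic Medications Titration Schema, which covers the EndoBarrier arm. Four of its sentences matter here:

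- **A, the default.** "Dosages of metformin will remain unchanged throughout the trial unless the sulfonylureas have already been discontinued", and in addition the "fasting blood glucose is documented under 5.6 mmol/L on 3 consecutive days". Both conditions must hold.
- **B.** "If the fasting blood glucose is under 5.6 mmol/L, metformin can be discontinued". The conditions in A are not repeated.
- **C.** "If the fasting glucose is below 3.5 mmol/L then metformin should be discontinued". Again neither condition is repeated.
- **D.** "If hypoglycaemic episodes are experienced, it is at the Investigator's discretion to modify or discontinue metformin".

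Between C and D comes a cross-reference: "See section 5.1 regarding blood glucose measurements". The section of that number is "5.1 Recruitment and Screening".

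Three other places bear on the point. The sulfonylurea paragraph just above requires the dose to be halved at implant, and halved again (or stopped if already at the lowest dose) after a hypoglycaemic episode. Section 5.5.1 describes glucose measurement and diabetes review for both arms. The Rescue Therapy paragraph says that medication changes will be discussed with a central diabetologist coordinator.

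**The concern.** Sentence A is worded as a closed rule: no change to metformin unless two things are both true. Sentence C calls for a change on a single criterion. The text does not say whether C is an exception to A or a further step that applies only once A's conditions are met.

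The patient for whom this matters is not unusual in design terms. A patient who enters on metformin plus a sulfonylurea has the sulfonylurea halved at implant, so is expected to be still taking one afterwards. That is the state in which A blocks any change.

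At stake is a written rule for responding to low fasting glucose, used at two sites. Metformin decisions also feed a secondary endpoint directly (reduction in dose or number of medications) and can affect HbA1c, on which the primary endpoint is based. A rule that can be followed in two ways is a possible source of inconsistency in both.

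**Working it through.** There is no stated figure to reproduce. Two checks apply: the sentences set side by side, and the visit schedule.

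**1. Applying the sentences literally.** Two fasting values are used for illustration: 5.0 mmol/L (below 5.6 only) and 3.2 mmol/L (below both thresholds).

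| Sulfonylurea | Days documented | Glucose (mmol/L) | A | B, read alone | C |
|---|---|---|---|---|---|
| Still taken | 1 | 5.0 | unchanged | can stop | – |
| Still taken | 1 | 3.2 | unchanged | can stop | should stop |
| Still taken | 3 | 5.0 | unchanged | can stop | – |
| Still taken | 3 | 3.2 | unchanged | can stop | should stop |
| Stopped | 1 | 5.0 | unchanged | can stop | – |
| Stopped | 1 | 3.2 | unchanged | can stop | should stop |
| Stopped | 3 | 5.0 | change allowed | can stop | – |
| Stopped | 3 | 3.2 | change allowed | can stop | should stop |

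At 3.2 mmol/L, A and C conflict in three of the four states. They agree only when the sulfonylurea has been stopped and three days are documented.

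**2. Trying a charitable reading.** If B is taken to inherit A's conditions, the apparent conflict at 5.0 mmol/L goes away, and B and C become graded steps (*can*, then *should*). That leaves C, with two possibilities:

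- C also inherits A's conditions. Then a value below 3.5 mmol/L triggers nothing under C while a sulfonylurea is still taken.
- C stands alone. Then the default in A is not true as written, because there is a further exception that it does not mention.

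The two readings lead to different actions for the same patient, and the text does not choose between them.

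**3. Sentence D.** Its trigger is a hypoglycaemic episode, not a fasting value, and the protocol does not define the term. If a reading below 3.5 mmol/L is regarded as an episode, D makes discretionary what C says should be done. This is tension, not contradiction, because D permits discontinuation.

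**4. Patients never on a sulfonylurea.** Inclusion criterion 3 asks only for oral T2DM medication and allows metformin, so metformin alone is eligible. Such a patient has no sulfonylurea that could already have been discontinued. The condition can reasonably be read as met, but the protocol leaves this to inference.

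**5. Why the cross-reference matters.** The three-day criterion cannot be documented from scheduled samples. By Table 2 and Table 4, the closest three successive post-implant fasting samples are V5, V6 and V7. V5 is at 10 days ± 3; V7 is at 3 months ± 7 days. With a month of 365.25/12 = 30.44 days and the windows used fully:

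- latest V5: 10 + 3 = 13 days
- earliest V7: 3 × 30.44 − 7 = 84.3 days
- shortest span: 84.3 − 13 = 71.3 days

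The criterion therefore depends on readings taken between visits. The reader who looks these up in section 5.1 finds recruitment, consent and screening, with no rule on glucose self-measurement. The text that applies is in 5.5.1.

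**The case against.** The strongest reply is that clinicians will not be misled. *Can* and *should* read naturally as graded steps, and the sulfonylurea condition plainly means that no sulfonylurea is left to reduce first. For a patient on a sulfonylurea, the paragraph above already requires a reduction or stop after a hypoglycaemic episode, so hypoglycaemia is not left unmanaged. The coordinator gives a central check across the two sites. Much of this stands and limits the practical consequence. It does not settle which of A and C prevails. The coordinator clause, read literally, covers changes in medication, and a site that follows A makes none.

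Two stronger readings are tempting and should not be drawn.

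- *That the three-day criterion relies on home readings these patients do not get.* Section 5.5.1 says "Home blood glucose meter readings will be indicated, as in routine clinical practice, when patients are clinically suspected or at risk of hypoglycaemic episodes", and stopping there suggests a narrow provision. The same sentence goes on to include readings needed to titrate therapy further. The section also covers reviews in the EndoBarrier arm and uses self-measurements to adjust medication. A metformin decision falls within that.
- *That the section gives three incompatible instructions.* D has a different trigger and allows the action in C. The outright conflict is between two sentences, A and C.

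It is also fair to object that no effect on an endpoint is demonstrated. The protocol gives no estimate of how many device patients would fall below 3.5 mmol/L while on metformin, in a population entering with HbA1c of 7.5–11.0%.

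**Conclusion.** The metformin rule contradicts itself as written. For a device patient with a fasting glucose below 3.5 mmol/L, the default sentence and the 3.5 mmol/L sentence give opposite instructions in three of the four combinations of sulfonylurea status and days documented. Reading the middle sentence charitably does not remove this. The discretion sentence adds tension if the reading is regarded as a hypoglycaemic episode, and the position of patients never on a sulfonylurea is unstated. The reference to section 5.1 is wrong; the text meant is in 5.5.1.

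The conclusion rests only on the wording and assumes no event rate. It is a correctable inconsistency in a rule that bears on patient safety. The possible influence on the HbA1c and medication endpoints is plausible, but its size cannot be derived from the protocol. Which sentence is clinically right is not judged here.

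**What to change.** The clinical leads should reconcile the metformin sentences in section 5.5.2 into one ordered rule that states:

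- which sentence takes precedence when fasting glucose is below 3.5 mmol/L and the conditions of the default sentence are not met;
- how the discretion sentence relates to that instruction when the reading is regarded as a hypoglycaemic episode;
- how the sulfonylurea condition applies to a patient who has never taken one.

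The cross-reference should be changed from 5.1 to 5.5.1.

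No threshold, dose or monitoring rule is proposed. The cost is protocol wording, submitted for ethics approval as section 11.3.2 requires of amendments; no visit, sample or analysis changes.

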### 5.5.3 Dietetic Input

#### Dietary counselling on diet and physical activity

At visit 2, all patients history and current eating behaviour will be assessed using the following information: anthropometry, biochemistry, co-morbidities, medication, activity level, eating habits including eating disorders and emotional eating, previous diets, lifestyle including smoking, drug and alcohol misuse, weight history, psychiatric history, family history of obesity, diabetes, mental illness or eating disorders, family history and available support network, work status, readiness and motivation for change, and understanding of both study arms.

At visit 2 and 4 (visit 4 control arm only) patients will receive diet and physical activity counselling by a qualified dietitian according to local standards. The dietary counselling programme intends to provide each subject with lifestyle and behavioural modification information, and good eating practices. On visit 2, all subjects in the Treatment arm will receive written information on how their diet will change after EndoBarrier insertion and written information will be provided for the liquid diet (see below) pre- and post- EndoBarrier insertion. They will also receive specialised advice for eating with their EndoBarrier after the liquid diet phase. Subjects in the control arm will be required to follow the same liquid diet as the EndoBarrier arm in order to standardise the groups. At visit 2, the control arm will also receive written information on how to follow the liquid diet. On visit 4 the control arm will receive information on how to follow a low calorie diet after the liquid diet ends (see below).

#### Liquid diet

In order to treat both study arms (control and treatment arm) equally all subjects will follow a liquid diet (based on milk, flavoured milk or milk replacements, water, low-sugar squashes, smooth/ clear soups, vegetable juices, tea or coffee without sugar, or unsweetened puree fruit juice) during the 7 days before and 13 days ( $\pm$  3 days) after the intervention visit (visit 4).

Subjects in the EndoBarrier arm will also receive information on food exclusions, tips for eating and drinking, use of vitamin and mineral supplements, and long-term dietary considerations.

|                                                                                   |                                                                             |                                    |                                               |                                            |
|-----------------------------------------------------------------------------------|-----------------------------------------------------------------------------|------------------------------------|-----------------------------------------------|--------------------------------------------|
| [figure not shown] | Title:
EndoBarrier TM
Gastrointestinal Liner
Diabetes Trial | Protocol No:
Version 5.0 | Sponsor:
Imperial College
London | Date:
5 th March 2018 |
|-----------------------------------------------------------------------------------|-----------------------------------------------------------------------------|------------------------------------|-----------------------------------------------|--------------------------------------------|

After the liquid diet, subjects in both study arms are advised to follow a low-calorie diet which is based on the guidelines below.

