### **Improves glycaemic control by:**

- Decreasing hepatic insulin resistance (and therefore hepatic glucose output) independently of any caloric restriction and before weight loss has taken place
- Increasing insulin production before and after weight loss has taken place
- Gradually decreasing total body and tissue specific insulin resistance as a result of weight loss
- Reducing visceral adiposity and hepatic and pancreatic fat content

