### 5.5.14 Metabolomics

Plasma, urine and faecal samples for metabolomics will be collected at visit 3, 5, 8 and 10 and 14.

Pre-labelled urine and faeces collection kits described below will be given to patients on all visits prior to collection.

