### 5.6.4 Gut hormones and metabolites (sub-groups 1-3)

In addition to the routine biochemistry and haematology, venous blood samples will be taken at intervals by venepuncture through a cannula placed in the antecubital fossa. No more than 110 mls will be taken for these on each visit. Serial plasma levels of glucose and other metabolites, bile acids, glucose, insulin, leptin, gut hormones (including ghrelin, GLP-1, PYY), adipocytokines and markers of insulin resistance, and inflammation will be measured. Assays will be performed by the Dept. of Chemical Pathology at Imperial College Healthcare NHS Trust and by in-house assays, outside contracts and commercial kits for radio-immunoassay and ELISA. For sub-groups 1 – 3 these will be measured when fasted during study visits 3, 5, 8, 10 and 14. For sub-groups 1 and 3 these will also be measured after a fixed/test meal at visit 3, 5, 8 and 10 (except for visit 14). A fixed meal will be a fixed amount of food e.g. (Fortisip compact®, Nutricia, Wiltshire, UK; 250 mL, 600 kcal, 24.0 g protein, 74.2 g carbohydrates, and 23.2 g fat). A test meal will be a commercially available food

|                                                                                   |                                                                             |                                    |                                               |                                            |
|-----------------------------------------------------------------------------------|-----------------------------------------------------------------------------|------------------------------------|-----------------------------------------------|--------------------------------------------|
| [figure not shown] | Title:
EndoBarrier TM
Gastrointestinal Liner
Diabetes Trial | Protocol No:
Version 5.0 | Sponsor:
Imperial College
London | Date:
5 th March 2018 |
|-----------------------------------------------------------------------------------|-----------------------------------------------------------------------------|------------------------------------|-----------------------------------------------|--------------------------------------------|

product served to excess that the patient will be instructed to eat until they feel comfortably full. For sub-group 2, only fasted measurements will be taken.

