### **5.6.10 Insulin clamp (sub-group 2 only)**

On visit 3, 5, and 8, patients will undergo a euglycaemic hyperinsulinaemic clamp with stable isotope infusion to determine overall insulin and compartment-specific insulin sensitivity (liver, muscle and adipose depot)

On the days prior to the clamp procedure patients' glucose-lowering medications will be adjusted by a research nurse or a clinician in order to avoid their interference with the clamp measurements. Patients will attend the research facility either the day prior to the study visit and stay overnight for an insulin sliding scale or they will attend the research facility in the morning after an overnight fast depending on their capillary glucose readings on the days before the clamp. Patients will be instructed to consume a standardised meal or meal replacement the evening prior to their study visit. A venous catheter will be inserted into a vein of each arm on the study morning. The first cannula will be used for infusions and the other for blood sampling. If blood glucose levels are higher than 6 mmol/l on arrival a variable rate insulin infusion will be started to attain a stable glucose level (4.0 -6.0 mmol/l) prior to commencement of the hyperinsulinaemic euglycaemic clamp. A primed continuous infusion of [6, 6-H2] glucose, a stable isotope tracer, will be started and maintained for 7 hours. Two hours later a two-stage hyperinsulinaemic-euglycaemic clamp procedure will be started and continued for 5 hours. During stage 1 of the clamp procedure, in which hepatic insulin resistance is assessed, insulin will be infused at a low dose (depending on patient's weight/body surface area) for 2 hours. During stage 2 of the clamp procedure, in which peripheral insulin

|                                                                                   |                                                                                                  |                                           |                                                             |                                                  |
|-----------------------------------------------------------------------------------|--------------------------------------------------------------------------------------------------|-------------------------------------------|-------------------------------------------------------------|--------------------------------------------------|

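### The late edge of the Visit 3 baseline window meets the start of the compulsory liquid diet, and nothing requires the mechanistic baseline to be taken before the diet begins

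*Protocol*

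**What the plan says.** Three parts of the protocol bear on this.

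- **Visit windows (section 5.3, Table 2).** Visit 3 is a baseline visit at minus 2 weeks ±7 days. Visit 4, when the device is implanted or the control regimen starts, is at week 0 ±3 days.
- **Diet (section 5.5.3).** "In order to treat both study arms (control and treatment arm) equally all subjects will follow a liquid diet", and this runs "during the 7 days before and 13 days" (±3 days) after Visit 4. The dietary counselling text makes it compulsory for controls too: "Subjects in the control arm will be required to follow the same liquid diet as the EndoBarrier arm".
- **Assessments at Visit 3.** For the clamp, section 5.6.10 says "On visit 3, 5, and 8, patients will undergo a euglycaemic hyperinsulinaemic clamp with stable isotope infusion". For gut hormones, section 5.6.4 says "For sub-groups 1 – 3 these will be measured when fasted during study visits 3, 5, 8, 10 and 14". For metabolomics, section 5.5.14 says "Plasma, urine and faecal samples for metabolomics will be collected at visit 3, 5, 8 and 10 and 14". Table 2 adds bioelectrical impedance, fMRI, taste and food preference testing, food diaries and 24-hour dietary recall. None of these has another measurement before Visit 4.

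The mechanism to be tested is set out in section 1.4: "Decreasing hepatic insulin resistance (and therefore hepatic glucose output) independently of any caloric restriction and before weight loss has taken place". No sentence in the visit schedule, the diet text or the procedure descriptions says that Visit 3 must come before the diet starts.

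**The concern.** The hypothesis is about an effect that occurs "independently of any caloric restriction and before weight loss has taken place". A baseline for it should describe the patient before any study-imposed restriction. If some Visit 3 assessments fall on the diet and most do not, the baseline mixes two dietary states, and change from baseline means different things in different patients.

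Section 8.2 plans comparisons within as well as between groups for the clamp, gut hormone and food preference outcomes. The within-group comparisons have no concurrent control to absorb such a shift. Dietary intake is the most directly exposed outcome, because a recall or diary taken on the diet records the prescribed liquids as habitual baseline intake.

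The protocol itself treats a few days as a relevant timescale: section 1.2 cites a comparison of surgery with caloric restriction at 4 days. The clamp and taste sub-groups have a minimum of 18, so even one or two such baselines would be noticeable.

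**Working it through.** The protocol gives no figure to reproduce, so the check is a calendar count in whole days, with planned Visit 4 as day 0.

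**Inputs**
- Visit 3: −14 ±7, so day −21 to day −7 (Table 2).
- Visit 4: 0 ±3, so day −3 to day +3 (Table 2).
- First diet day: Visit 4 minus 7 (section 5.5.3).

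**Formulas.** Let gap = Visit 4 day − Visit 3 day.
- Visit 3 is on a diet day if gap ≤ 7.
- Completed diet days before Visit 3 = max(0, 7 − gap).

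**Case A: the windows run from the actual Visit 4 date.** The smallest gap is 14 − 7 = 7. Completed diet days = 7 − 7 = 0. The two rules share only day −7, the first diet day.

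**Case B: Visit 3 is scheduled from a planned day 0, and the diet from the date on which Visit 4 is held.**

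| Visit 4 held on day | First diet day | Compliant Visit 3 days on the diet | Most completed diet days |
|---|---|---|---|
| −3 | −10 | −10 to −7 (4 days) | 3 |
| −2 | −9 | −9 to −7 (3 days) | 2 |
| −1 | −8 | −8 to −7 (2 days) | 1 |
| 0 | −7 | −7 (1 day) | 0 |
| +1 to +3 | −6 to −4 | none | none |

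The smallest gap is (−3) − (−7) = 4 days, which gives 7 − 4 = 3 completed diet days.

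There are 15 × 7 = 105 allowed date pairs. Of these, 4 + 3 + 2 + 1 = 10 (9.5%) put Visit 3 on a diet day, and 3 + 2 + 1 = 6 (5.7%) put it after at least one completed diet day. These are counts of permitted calendar combinations, not of patients.

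**At the nominal time.** With Visit 3 on day −14, the earliest possible diet start is day −10, 4 days later. The overlap is confined to the late edge of the window.

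**Primary endpoint.** Table 4 takes HbA1c at Visit 1 and not at Visit 3, so the HbA1c baseline is not involved.

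**The case against.** The case on the other side is substantial.

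- **Anchoring.** The protocol does not say that Visit 3 is counted from a notional day 0 while the diet follows a different actual date. Patients get written diet instructions at Visit 2 and would probably start from the booked Visit 4 date. If Visit 4 were then brought forward, the diet would be shortened; it would not have begun earlier. This stands as a reason to treat the three-day overlap as conditional. It does not remove the point, because a ±3-day window on Visit 4 implies a planned reference date, and day −7 is shared on either reading.
- **Fasting.** Routine bloods follow an 8-hour fast and the clamp an overnight fast, so an assessment on the first diet day largely precedes that day's intake. This limits the effect for blood measures when no diet day has been completed. It helps less once diet days have been completed. Food diaries are kept around each visit, so any diary days after a Visit 3 on day −7 would fall on the diet.
- **The control arm.** Both arms follow the same diet, and Visit 5 (day 10 ±3) nominally falls within the post-Visit 4 diet in both. Caloric restriction is thus handled mainly by the concurrent comparison, including the group-by-time interaction for fMRI. This stands. The between-arm contrast does not depend on a diet-free baseline in the way that within-arm change does.
- **Existing records.** Food diaries and dietary recall may already show who was on the diet at Visit 3. That helps detection but does not prevent the overlap.

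**Conclusion.** The point holds as a scheduling gap of limited reach. A protocol-compliant Visit 3 can fall on the first day of the liquid diet. It can follow up to three completed diet days if Visit 3 is scheduled from a planned day 0 and Visit 4 is held early. The result would be a mixed mechanistic baseline in a few patients, blurred within-arm change and some added noise.

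A reader might infer three stronger things, and the documents support none of them.

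- **That about 9.5% of patients are affected.** That figure treats all 105 date pairs as equally likely, for which there is no basis. Four of the ten overlapping pairs also involve no completed diet day.
- **That the comparison between arms is biased**, for instance because implantation depends on theatre availability. Both arms have the same windows and the same diet, and nothing shows that the Visit 3 to Visit 4 gap differs by arm.
- **That the primary result is at risk.** It is not, because its baseline is not taken at Visit 3.

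**What to change.** Reconcile Table 2 with section 5.5.3 by stating that all Visit 3 assessments are completed before the liquid diet starts, that is, at least 8 days before the booked Visit 4. Say which date the windows are counted from, and record the diet start date. The diet itself does not change.

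For patients already past baseline, use the visit dates, which section 12.1 already requires as source data. Flag those with a Visit 3 to Visit 4 gap of 7 days or less, and run a sensitivity analysis of the mechanistic outcomes without them.

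The cost is a slightly narrower late side of one visit window. With Visit 4 booked on day 0, the last permitted day moves from −7 to −8. If Visit 3 is counted from a planned day 0 and Visit 4 is booked 3 days early, it moves from −7 to −3 − 8 = −11, a loss of 4 days.
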